### Trial dropouts and missing data

Because participation in the trial is voluntary, patients can leave the trial at any time for any reason if they wish to do so without any consequences. No or minimal losses to follow − up for the primary and secondary outcomes are anticipated. Complete–case analysis will be carried out for all the outcomes, that is, excluding patients with missing data in the outcome of interest. However, if any missing data is found for the primary outcome, a sensitivity analysis using multiple imputations and estimating − equation methods will be performed.

### Handling of data

All patient’s identifiable personal data will be separated from the research data and replaced by an assigned code. Data will be obtained from the electronic patient record and entered into the electronic case report form stored in Castor [19], a good clinical practice − compliant web–based data management system. The handling of personal data adheres the general data protection regulations and applicable national laws. After completing the data collection, full access to the database will be granted to selected investigators. Data are restricted available after analyses and publication of the main paper. All data will be stored in a secure place for 15 years after study end. The results of GENERATOR will be published in scientific journals and used for national and international guidelines. A summary of the results will be placed on ClinicalTrials.gov to inform participants.

### Sample size calculation

The required sample size is calculated based on an estimated effect size derived from individual patient data from previous clinical trials [6, 21, 22]. Based on a recently published randomized clinical trial [15], we conservatively estimate an incidence of PPCs of 30% in the standard low PEEP without RMs group. To have a power of 80% to detect a relative risk reduction in the incidence of PPCs of 20% (24% vs 30%), given an alpha of 0.05, 860 patients in each group are needed. Assuming a dropout rate of 5%, 903 patients per group are needed, resulting in a total sample size of 1806 patients.

### Statistical analysis

Before completion of recruitment, a complete statistical analysis plan will be made available online. All statistical analyses will be conducted according to the modified intention–to–treat (ITT) principle considering all patients in the treatment groups to which they were randomly assigned, excluding those lost to follow–up due to consent withdrawal or surgery cancelation. Baseline characteristics for both arms will be presented as counts and percentages, means and standard deviations (SD), or medians and interquartile ranges (IQR), depending on the normality of data distribution. Hypothesis tests will be two–sided with a statistical significance level of 5% (i.e., *p* < 0.05) for all outcomes. No adjustments will be made for the *p*–value for multiple comparisons. Statistical analysis will be performed using the free software program “R” (R Core Team, 2020, Vienna, Austria).

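### The modified ITT exclusion does not separate withdrawal before surgery from withdrawal after the allocated ventilation and, read literally, keeps withdrawn patients out of the planned imputation analysis

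*Protocol article*

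**What the plan says.** Three sections of the protocol article bear on this point.

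- **Statistical analysis.** Every analysis follows a modified intention-to-treat principle. Patients stay in their randomised group, except those lost to follow-up "due to consent withdrawal or surgery cancelation". Nothing limits this to events before surgery or before ventilation.
- **Trial dropouts and missing data.** Participation is voluntary and "patients can leave the trial at any time for any reason". Few or no losses are expected. Each outcome is analysed on complete cases, but "if any missing data is found for the primary outcome, a sensitivity analysis using multiple imputations" and estimating-equation methods is added.
- **Trial endpoints.** The primary endpoint is a composite of pulmonary complications (PPCs) to postoperative day 5, and it is met at the first PPC.

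The sample size section adds 5% for dropout. It does not say how much of that is cancellation, withdrawal before surgery or withdrawal afterwards.

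**The concern.** The exclusion joins two situations that differ in kind. If surgery is cancelled, the patient receives no trial ventilation and the allocation cannot have affected the outcome, so leaving that patient out does little harm to the comparison. Withdrawal can come at any time, including after ventilation, when the allocated strategy may already have influenced recovery and recovery may influence the decision to leave. Removing such patients is a post-randomisation exclusion that may depend on outcome.

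The imputation analysis is the natural check on this. But it is itself one of the analyses governed by the modified ITT rule. Read literally, patients lost through withdrawal are gone before imputation starts, so it cannot show what their removal did. The missing-data section, which opens with voluntary leaving and is triggered by any missing primary outcome, suggests the opposite. Two analysts could therefore build different analysis sets from the same text.

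**Working it through.** **1. The plan's own figure.** Inputs from Sample size calculation and Statistical analysis: 30% v 24%, two-sided alpha 0.05, power 80%, 1:1 allocation. With pooled variance under the null:

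n = [1.960 × √(2 × 0.27 × 0.73) + 0.842 × √(0.30 × 0.70 + 0.24 × 0.76)]² / 0.06² = 859 per group.

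The protocol states "given an alpha of 0.05, 860 patients in each group are needed", so the figure reproduces. It then takes 860 × 1.05 = 903 per group. Five per cent of 903 is about 45 patients per group, leaving 858.

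**2. The rules side by side.**

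- Who is removed: those lost to follow-up through withdrawal, at any time.
- From what: every analysis.
- When imputation applies: any missing primary outcome.

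Consider a patient who is ventilated as allocated, is event-free on day 1 and withdraws on day 2. The first two rules take the patient out. The third would take the patient in, because the day-5 outcome is missing. The text does not say which prevails.

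**3. From analysed set to full set.** Suppose the analysed patients show 30% v 24%, and a fraction d of each arm was excluded after treatment. The full-set rate per arm is (1 − d) × analysed rate + d × rate among the excluded. The protocol gives neither d nor the rates among the excluded, so the values below are assumptions.

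- d = 5%, excluded rates 60% (intervention) and 30% (control): control 0.95 × 0.30 + 0.05 × 0.30 = 0.300; intervention 0.95 × 0.24 + 0.05 × 0.60 = 0.258. Difference 4.2 points, relative reduction 0.042/0.300 = 14%.
- d = 5%, excluded rate 60% in both arms: 0.315 − 0.258 = 5.7 points.
- d = 1%, excluded rates 60% and 30%: 0.300 − (0.99 × 0.24 + 0.01 × 0.60) = 0.300 − 0.2436 = 5.6 points, relative reduction 18.8%.
- Extreme bounds at d = 5% (no events among one arm's exclusions, all events among the other's): 0.285 − 0.278 = 0.7 points, and 0.335 − 0.228 = 10.7 points.

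**4. Effect on false positives.** Assume no true effect (30% in both arms), 903 per arm and m excluded per arm. Excluded controls have the average rate; excluded intervention patients have rate r. The analysed intervention rate is (0.30 × 903 − r × m)/(903 − m). The rejection rate is for a two-sided 5% test with 903 − m per arm.

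| Excluded per arm | r | Analysed intervention rate | Spurious difference | Rejection rate |
|---|---|---|---|---|
| 9 (1%) | 50% to 100% | 29.8% to 29.3% | 0.2 to 0.7 points | 5.1% to 6.2% |
| 18 (2%) | 50% to 100% | 29.6% to 28.6% | 0.4 to 1.4 points | 5.4% to 10.1% |
| 45 (5%) | 50% to 100% | 29.0% to 26.3% | 1.1 to 3.7 points | 7.6% to 39% |

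With r = 30% there is no bias at any m.

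**The case against.** The strongest reply is that the rule is narrower than it looks, and that several stronger readings go beyond the text.

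- A reader might infer that **recorded events are thrown away**. The documents do not say so. The exclusion is worded for patients lost to follow-up, and the endpoint is met at the first PPC, so a patient with a PPC on record is arguably not lost for that endpoint. Handling of data collected before withdrawal is not stated either way.
- A reader might infer that **the complete-case rule drops patients with a PPC and missing later days**. It does not: their composite outcome is already settled and so is not missing.
- A reader might infer that **withdrawal is the main source of missing outcomes**. Nothing shows this. The 5% is not split by cause, few losses are expected, and daily follow-up that stops at discharge before day 5 could be another source. Imputation would still have those other gaps to work on.
- A reader might take **4.2 points as the likely effect**. That treats the whole 5% as treated patients, although it may include cancellations, and it needs strongly arm-dependent event rates among them. Patients, ward nurses and outcome assessors are blinded, which makes arm-dependent withdrawal less likely, and the primary window is only five days.

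All of this stands and limits the size of the point. It could also be said that such detail belongs in the statistical analysis plan, which is promised before recruitment ends and is not shown. That is fair for the imputation model and for further sensitivity analyses. It does not dispose of the point, because the article already states an exclusion rule that covers every analysis and has no time limit. This is a rule fixed too broadly, not an omitted detail.

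**Conclusion.** The point holds in a limited form. As worded, the modified ITT rule allows treated patients to be excluded after withdrawing and, read literally, puts them beyond the imputation analysis; the missing-data section points the other way.

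The practical effect is probably small. At 1% post-treatment withdrawal, or with equal event rates among the excluded in both arms, an analysed difference of 6.0 points corresponds to about 5.6 to 5.7 in the full set. It becomes material only if post-treatment withdrawal is both frequent and related to outcome differently in the two arms. The 14% relative reduction in place of 20%, and rejection rates of up to 39%, need the whole 5% to be such patients. All these figures rest on assumed withdrawal and event rates, since the protocol gives none. The correction is worth making because it is cheap and removes a choice that could otherwise be made after the data are seen.

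**What to change.** In Statistical analysis, limit the modified ITT exclusion to patients whose surgery was cancelled or who were never ventilated in the trial, which includes withdrawal before surgery. Keep all other randomised patients in their allocated group, using data up to withdrawal where consent allows, so that a PPC recorded before withdrawal counts as an event under the existing endpoint definition.

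In Trial dropouts and missing data, state that event-free patients who withdrew before day 5 are included in the imputation sensitivity analysis. Report by arm the number of patients whose data have to be deleted.

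The cost is a short change of wording in the protocol and the statistical analysis plan, and a little more analysis work. The required sample size does not change. If all 903 per group were kept with known outcomes, power would be 82.0%, against 80.0% with 858. Patients who require deletion of their data would still be left out, but their number would be visible.

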## Methods

### Objectives and design

This investigator − initiated, international, multicenter, prospective, two–group, patient and outcome-assessor blinded randomized clinical trial (RCT) tests the hypothesis that in patients scheduled for minimally invasive abdominal surgery and at increased risk for PPCs, an individualized high PEEP strategy, titrated to the lowest ΔP, with RMs prevents PPCs when compared to a ventilation strategy that uses standard low PEEP without RMs. We further hypothesize that the individualized high PEEP strategy with RMs shortens duration of hospital stay and reduces the associated healthcare costs. A total of 1806 patients will be recruited in 20 academic and community hospitals in The Netherlands, Germany, Austria, Spain, and Italy (Table 4 in Appendix 1). Included patients will be randomly allocated in a 1:1 ratio to one of two intraoperative mechanical ventilation strategies (*see* Consolidated Standards of Reporting Trials (CONSORT) diagram in Fig. 1). The study design of GENERATOR is based on the ongoing DESIGNATION trial conducted by our group [9].

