### Trial endpoints

The primary endpoint of GENERATOR is a composite of PPCs until postoperative day 5 as used before in the DESIGNATION trial [9]. A patient meets the endpoint upon experiencing at least one PPC. The composite comprises the following PPCs:(i)Mild respiratory failure, defined as the occurrence of one or multiple of the following conditions: peripheral oxygen saturation (SpO_2_) < 90% or partial pressure of oxygen in the arterial blood (PaO_2_) < 7.9 kPa (or < 50 mmHg) in room air, but responding to supplemental oxygen; a sudden increase in supplemental oxygen requirement to maintain adequate saturation (SpO_2_ > 90%) in patients receiving routine postoperative oxygen therapy; any level of supplemental oxygen after more than 2 days postoperatively;(ii)Severe respiratory failure, defined as need for noninvasive or invasive mechanical ventilation, or a PaO_2_ < 60 mmHg (or < 7.9 kPa) or SpO_2_ < 90% despite supplemental oxygen in spontaneously breathing patients;(iii)Bronchospasm, defined as newly detected expiratory wheezing treated with bronchodilators;(iv)Suspected pulmonary infection, defined as receiving antibiotics and meeting at least one of the following criteria: new or changed sputum, new or changed lung opacities on chest radiograph when clinically indicated, tympanic temperature > 38.3 °C, white blood cell (WBC) count > 12,000/μL;(v)Pulmonary infiltrate, defined as any unilateral or bilateral infiltrates on chest radiography;(vi)Aspiration pneumonitis, defined as respiratory failure after inhalation of regurgitated gastric contents;(vii)Atelectasis, defined as lung opacification with a shift of the mediastinum, hilum, or hemidiaphragm towards the affected area and compensatory overinflation in the adjacent non − atelectatic lung on chest radiography;(viii)ARDS, according to the “Berlin definition for ARDS” [20];(ix)Pleural effusion, defined as blunting of the costophrenic angle, loss of the sharp silhouette of the ipsilateral hemidiaphragm in upright position, evidence of displacement of adjacent anatomical structures or (in supine position) a hazy opacity in one hemithorax with preserved vascular shadows on chest radiography;(x)Cardiopulmonary edema, defined as clinical signs of congestion, including dyspnea, edema, rales, and jugular venous distention, with the chest radiograph demonstrating increase in vascular markings and diffuse alveolar interstitial infiltrates; and(xi)Pneumothorax, defined as air in the pleural space with no vascular bed surrounding the visceral pleura on chest radiography.

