
The secondary endpoints include:(i)Intraoperative complications, that are not related to induction or change of the depth of anesthesia, consisting of:◦ Any episode of desaturation, defined as SpO_2_ ≤ 90% or if preoperative SpO_2_ < 90% an absolute decrease in SpO_2_ > 5% and lasting > 1 min;◦ Any episode of hypotension defined as MAP 65 < mmHg and lasting > 1 min [17];◦ Any need for vasoactive agents, either as bolus or continuous administration, defined as more than needed to compensate for vasodilating effects of anesthesia as judged by the attending anesthesiologist;◦ Any new arrhythmias needing intervention as suggested by the ACLS guidelines [18];(ii)Intraoperative fluid strategy, including the total amount of fluids administered during anesthesia, including the amounts of colloids, crystalloids, and blood products;(iii)Postoperative extrapulmonary complications (*see* Appendix 2);(iv)All–cause mortality at day 5, day 30 and 90 after surgery and in − hospital mortality; and(v)Cost–effectiveness parameters including:◦ Presence and duration of postoperative supplemental oxygen;◦ Use of antibiotics for pneumonia;◦ Occurrence of imaging (chest x–ray; computed tomography scan);◦ Length of stay in hospital; and◦ Unplanned admission to an intensive care unit (ICU) (and if applicable, length of ICU admission).

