The main strengths of the current study are the large sample size, multicenter approach and pragmatic protocol design. GENERATOR will be conducted in both academic as non − academic hospitals in different countries in Europe, making the results generalizable. The main outcome measure, which is a composite of PPCs, is a clinically relevant endpoint that has been used in several clinical trials on intraoperative ventilation [21, 26, 28], as PPCs can be combined due to their shared underlying pathophysiological mechanisms. In addition, even so − called minor pulmonary complications are associated with an increased risk of mortality and length of hospital stay in surgical patients [4]. Therefore, the composite endpoint of PPCs has clinical significance and enhances the statistical power of the trial due to summation of incidences of single events. In GENERATOR, both the composite endpoint and the individual incidences of each specific PPC will be reported separately. Additionally, the trial will assess the impact of the intraoperative ventilation strategy on the occurrence of extrapulmonary complications as well as the length of stay in hospital and ICU. These secondary endpoints hold both clinical relevance and are essential to estimate the related health care costs.

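### About 25 secondary items may each be declared significant at an unadjusted 5% level, with no order among them and no exploratory label, even if the primary endpoint is negative

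*Protocol article*

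**What the plan says.** The protocol article names one primary endpoint under Trial endpoints: "The primary endpoint of GENERATOR is a composite of PPCs until postoperative day 5". The Sample size calculation is built on that endpoint alone.

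Under Statistical analysis, the testing rule covers every outcome: "Hypothesis tests will be two–sided with a statistical significance level of 5" per cent, "for all outcomes. No adjustments will be made for the *p*–value for multiple comparisons". The same section promises more detail later: "Before completion of recruitment, a complete statistical analysis plan will be made available online".

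Objectives and design adds a further hypothesis to the main one: "We further hypothesize that the individualized high PEEP strategy with RMs shortens duration of hospital stay and reduces the associated healthcare costs".

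Trial endpoints lists five secondary headings, the first being "Intraoperative complications, that are not related to induction or change of the depth of anesthesia". Each heading contains several separate measures. The Discussion says of the components of the primary endpoint that "both the composite endpoint and the individual incidences of each specific PPC will be reported separately".

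Nowhere does the article call the secondary endpoints exploratory, put them in a testing order, or make a claim on them depend on the primary result.

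**The concern.** Leaving secondary tests unadjusted is acceptable when they are presented as exploratory. Here that label is absent, while the significance threshold is explicitly extended to all outcomes. This is a rule the article fixes, not a detail it leaves open: a later analysis plan that merely follows it would carry the problem forward.

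The secondary results are also given weight. The Discussion calls the secondary endpoints clinically relevant and essential for estimating costs, and Handling of data says the results will be used for guidelines. With a negative primary, the rule as written would still permit a statement that hospital stay was significantly shorter, or that unplanned ICU admission was significantly reduced, on one unadjusted p-value among many.

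**Working it through.** **The plan's own figures.** The article states no familywise error rate, so there is none to reproduce. Its 0.05 enters the sample size for the primary endpoint, and that calculation does reproduce. For 30% against 24%, the mean proportion is 0.27, and

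n = [1.960·√(2·0.27·0.73) + 0.842·√(0.30·0.70 + 0.24·0.76)]² / 0.06² ≈ 859 per group, against 860 stated.

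Power at 860 per group is 80.1%. The primary endpoint thus has a full two-sided 5% to itself, and the secondary rule does not alter that.

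**Counting the secondary items** (Trial endpoints; Appendix 2 for the extrapulmonary definitions):
- intraoperative complications: desaturation, hypotension, vasoactive agents, arrhythmias = 4
- fluids: total, colloids, crystalloids, blood products = 4
- extrapulmonary complications: sepsis, septic shock, extrapulmonary infection, anastomotic leak, acute renal failure = 5
- mortality: day 5, day 30, day 90, in hospital = 4
- resource use: oxygen given, oxygen duration, antibiotics, chest x-ray, CT, hospital stay, unplanned ICU admission, ICU stay = 8

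Total: 4 + 4 + 5 + 4 + 8 = 25. The 11 individual PPCs are not counted, because the article says only that their incidences are reported.

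**Independent tests, all nulls true.** P(at least one p < 0.05) = 1 − 0.95^k.
- k = 25: 1 − 0.95^25 = 0.723, with 25 × 0.05 = 1.25 false positives expected
- k = 5 (headings only): 1 − 0.95^5 = 0.226
- the probability first passes one half at k = 14: 1 − 0.95^14 = 0.512

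**Correlated tests, all nulls true.** The documents give no correlations, so a range is assumed. Simulation of 200,000 sets of 25 normal test statistics with a common correlation gave:

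| Common correlation | P(at least one false positive) |
|---|---|
| 0.3 | 60.8% |
| 0.4 | 54.1% |
| 0.5 | 46.5% |
| 0.6 | 39.1% |
| 0.7 | 31.5% |

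Grouping the items by their five headings gives a similar range: 60.1% with correlation 0.5 within and 0.2 between groups, and 41.7% with 0.8 and 0.4.

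**Rare events.** At an assumed event rate of 0.5% and 860 per group, the true size of a nominal 5% test is 4.4% (chi-square) or 1.9% (Fisher). Rare outcomes therefore pull the figures down somewhat.

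**The case against.** The strongest reply is that one primary endpoint with openly unadjusted secondary tests is a recognised approach, and that labels and ordering are usually settled in the analysis plan, which the article promises. The authors also show caution about secondary results: the Discussion discounts an earlier trial's lower PPC incidence because PPCs were a secondary endpoint there. Part of this stands. The analysis plan can add the label, and nothing in the article announces an intention to claim secondary findings after a negative primary. But the article does more than stay silent: it extends the significance level to all outcomes and rules out adjustment. The remark about the earlier trial concerns power and does not bind this one.

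Four stronger readings are tempting, and the documents do not support them.

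- **That the trial has no hierarchy at all.** It has one primary endpoint, the sample size rests on it, and stay and costs are introduced as further hypotheses. What is missing is order and labelling among the secondary endpoints.
- **That the stated 5% is false.** The article sets a level per test and openly declines to adjust. It claims no familywise level.
- **That a false positive is more likely than not.** This needs every null to be true and correlations to be low to moderate. For 25 items the probability is already below one half at a correlation of 0.5. Many items overlap by construction: mortality at successive days is cumulative, septic shock is a subset of sepsis, and total fluids contain their parts.
- **That the 11 individual PPCs add 11 tests.** The article promises to report them, not to test them.

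The count of 25 is itself an unpacking of five headings. If the intraoperative complications, extrapulmonary complications and mortality measures were classed as safety outcomes (an assumption), 25 − 13 = 12 items would remain, and 1 − 0.95^12 = 46% under independence.

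**Conclusion.** The point holds for the secondary endpoints only. The primary endpoint's type I error and the sample size are untouched. As written, about 25 secondary items, length of stay among them, could each be declared significant at an unadjusted 5% level whatever the primary shows.

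If all nulls are true, the chance of at least one false positive is about 72% under independence and about 39% to 61% at assumed correlations of 0.6 down to 0.3. It is 23% if each of the five headings counts as one independent test. Every one of these is well above 5%, so the conclusion does not depend on which is preferred. The exact size does depend on the count, on the assumed correlations and on the global null. This is a worthwhile and cheap improvement, not a flaw in the main comparison.

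**What to change.** Replace the two sentences on significance level and multiplicity in the Statistical analysis section, and carry the same text into the analysis plan, so that they state:

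1. The two-sided 5% significance test is confirmatory for the primary endpoint only.
2. Length of hospital stay may be tested at 5% only if the primary endpoint is significant. This fixed sequence takes nothing from the primary.
3. All other secondary endpoints and the individual PPCs are reported as effect estimates with unadjusted 95% confidence intervals, labelled exploratory, with no claim of significance. Healthcare costs, the other half of the further hypothesis, would be estimated in the same way.
4. Outcomes named in advance as safety outcomes are also reported unadjusted, so that signals of harm are not suppressed. The list must be written down, since the article does not define one.

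No p-value correction is needed; a Bonferroni rule over 25 items would demand p < 0.05/25 = 0.002. The cost is one paragraph of wording, with no extra patients or data and no loss of power on the primary endpoint. The one real downside is that an isolated secondary p-value below 0.05 can no longer be claimed as a finding.
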